### Follow-up

After finishing the acupuncture treatments, patients will be followed up monthly via telephone for 1 year post randomization. Stroke recurrence, all-cause deaths and BP control will be investigated and recorded in the CRFs. The patients will be required to use the BP diaries to record their BP four times daily. If the BP is ≤ 160 mmHg systolic and/or ≤ 100 mmHg diastolic for 1 month, the patient will be advised to take antihypertensive medications, which will be documented in the CRF.

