The synergistic BP-lowering effectiveness of acupuncture and antihypertensive agents has been proven, despite there formerly being insufficient evidence for acupuncture alone in lowering BP [22]. Recently, researchers have reported some positive results regarding sole acupuncture treatment for hypertension [23–25]. The reasons for this paradoxical situation could be disparities in acupuncture manipulation skills as well as other technical factors. Considering the limited reporting quality, the effect of pure acupuncture in lowering BP remains elusive.

Given that complementary and alternative interventions are recommended for mild and moderate hypertensive patients [26], we cautiously decided to select the hypertensive patients with uncontrolled BP (systolic BP ≥ 140 and < 160, or/and diastolic BP ≥ 90 and < 100 mmHg) who were taking one class of antihypertensive drugs to be the participants. The difference between the control and experimental groups is that in our experimental group, after a period of BP-lowering acupuncture add-on treatment, i.e., the “*HuoXueSanFeng*” needling method which has been proved to positively treat primary hypertension [27–33], if the BP falls below 140/90 mmHg, the prior antihypertensive drugs will be ceased, so as to observe the clinical effects of pure acupuncture on BP. Moreover, aiming to create a situation that is analogous to the real world, antihypertensive drugs will be adjusted based on the patients’ BP readings (detailed in the “Antihypertensive medication adjustment” section below) in both groups, respectively.

Altogether, our team conceived this high-quality, pragmatic randomized controlled clinical trial with the primary objective to determine whether BP-lowering acupuncture add-on therapy could decrease the recurrence of first-time ischemic stroke in patients during the 9-month follow-up period.

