## Methods/design

### Study design and setting

Our study is a prospective, multicenter, subject-, assessor-, and analyst-blinded, pragmatic randomized controlled trial. The research period lasts from May 2015 to May 2020 (201507001-08). Five centers from five cities will be involved in recruitments, treatments, and assessments. Informed consent will be obtained after screening for eligibility, then baseline assessments will be conducted before randomization (details in Table 1). Eligible patients will be allocated, in a 1:1 ratio using a dynamic randomization procedure, into a BP-lowering acupuncture therapy group (experimental group) and a control group. After randomization, the patients in the experimental group will be additionally treated by the *HuoXueSanFeng* needling method (a BP-lowering regimen) plus the “*XingNaoKaiQiao*” needling method [34] (a formula for stroke) over 12 weeks, whereas the control group will be only given the *XingNaoKaiQiao* needling method for 12 weeks. Other routine ischemic stroke treatments in both groups will be provided. During the whole process of our study, the antihypertensive medications will be adjusted based on the BP level in the two groups (details displayed in the “Antihypertensive medication adjustment” section). The primary outcome will be all recurrent stroke cases over a follow-up period of 9 months after receiving 12-week acupuncture treatments. Our protocol presentation is in accordance with the Standard Protocol Items: Recommendations for Interventional Trials 2013 (SPIRIT 2013) guidelines. The study flowchart is presented as Fig. 1.

**Table 1 Tab1:** Study schedule

Period	Screening	Baseline	Treatment (weeks 1–12)		Follow-up (weeks 13–48)	
Week	Week 0	Week 0	Week 6	Week 12	Week 24	Week 48
Eligibility	×					
Demographic medical history	×					
Informed consent		×				
Basic laboratory test®	×			×	×	
24-h ABPM		×	×	×		
TCM syndrome score, SF-36		×	×	×		
NIHSS, BI		×	×	×		
ESRS		×				×
Follow-up BP					×	×
Recurrence of stroke						×
NO, ET, Hcy, sCD40L, Copeptin		×		×	×	
ECG		×		×	×	
Chest X-ray		×				
Color Doppler ultrasound®		×		×		
All-cause mortality rate						×
Combined diseases and drugs	Record at any time					
Antihypertensive medication adjustment	Record at any time					
Adverse event	Record at any time					
Daily BP	Record everyday (based on BP diary)					
Safety of acupuncture	Record at any time					
Patients’ compliance				×		

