### Antihypertensive medication adjustment

After randomization, an electronic BP machine and a BP diary notebook will be delivered to all patients for measuring and recording their BP levels. During the first 6-week inpatient treatments, they will be instructed how to use the machine accurately. BP will be measured within 1 h after morning waking before taking antihypertensive medications, at 3 h after taking antihypertensive medications, at 4 p.m. and before bedtime over the entire process. On each occasion, three repeated measurements of supine BP, following a rest of at least 15 min, will be conducted at 1-min intervals. The antihypertensive medication classes in both groups will be recorded. Lifestyle advice regarding hypertension and stroke will be given to the patients. In the experimental group, if the patients have a mean BP level below 140/90 mmHg for three consistent days, they will receive solely acupuncture treatment; thereafter, once their BP levels increase to ≥ 140 mmHg systolic and/or ≥ 90 mmHg diastolic for 1 month, prior antihypertensive medications should be re-dispensed. Otherwise, if BP levels are ≥ 160 mmHg systolic and/or ≥ 100 mmHg diastolic for three consistent days after initiating *HuoXueSanFeng* acupuncture treatments or over the follow-up period, additional antihypertensives should be prescribed. All the medication adjustments will be filled out in the Case Report Forms (CRFs).

For the control group, when the average systolic BP increases to ≥ 160 mmHg and/or diastolic BP ≥ 100 mmHg lasting for three continuous days in the study period, other antihypertensive drugs will be prescribed in the opinion of the treating physicians, and these will be documented for final analyses.

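### The follow-up blood pressure rule for antihypertensive drugs is wrong as written and contradicts the rule that keeps controlled experimental patients off drugs

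*Protocol article*

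**What the plan says.** Two sections of the Protocol article govern antihypertensive drugs after randomisation.

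**Antihypertensive medication adjustment.**
- Stop rule, experimental arm only: "if the patients have a mean BP level below 140/90 mmHg for three consistent days, they will receive solely acupuncture treatment".
- Restart rule for those patients, once their readings "increase to ≥ 140 mmHg systolic and/or ≥ 90 mmHg diastolic for 1 month, prior antihypertensive medications should be re-dispensed".
- Step-up rule, experimental arm: an additional drug "if BP levels are ≥ 160 mmHg systolic and/or ≥ 100 mmHg diastolic for three consistent days". This sentence names the follow-up period explicitly.
- Step-up rule, control arm: the same 160/100 limits, "lasting for three continuous days in the study period, other antihypertensive drugs will be prescribed".

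The Background repeats the stop rule, "if the BP falls below 140/90 mmHg, the prior antihypertensive drugs will be ceased"; its stated purpose is to see what acupuncture alone does to blood pressure. The section on study design and setting gives the scope: "During the whole process of our study, the antihypertensive medications will be adjusted based on the BP level in the two groups".

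**Follow-up.** For the months after acupuncture ends, one sentence sets a further rule: "If the BP is ≤ 160 mmHg systolic and/or ≤ 100 mmHg diastolic for 1 month, the patient will be advised to take antihypertensive medications". It gives no lower limit and names no arm.

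**The concern.** The follow-up inequality points the wrong way for a rule that starts treatment. Read as printed, it reaches patients whose pressure is normal and misses those above both limits. It also cuts across the stop and restart rules, which leave an experimental patient off drugs for as long as pressure stays below 140/90.

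Antihypertensive treatment is a co-intervention that can affect stroke recurrence; the Background itself calls hypertension an independent risk factor for recurrence. The follow-up rule operates during the 9 months in which recurrent strokes are counted for the primary outcome. Only the experimental arm has a stop rule, so the direct conflict falls on that arm alone. If sites resolve it differently, drug exposure in that arm will vary by site for reasons unrelated to the treatment strategy. The diary blood pressures, which the statistical methods compare at 6 months and 1 year, would be affected in the same way.

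**Working it through.** There is no plan figure to reproduce here. The sample size, power and significance level do not enter. The check applies each rule to example readings.

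**Inputs**
- Adjustment section, experimental patient off drugs: stay off if systolic < 140 and diastolic < 90; restart after 1 month if systolic ≥ 140 and/or diastolic ≥ 90; add a drug after three days if systolic ≥ 160 and/or diastolic ≥ 100.
- Follow-up section, as printed: advise drugs after 1 month if systolic ≤ 160 and/or diastolic ≤ 100.
- Two possible repairs, neither stated in the article. (a) Reversed sign: systolic ≥ 160 and/or diastolic ≥ 100 for 1 month. (b) Missing lower bound: systolic ≥ 140 and/or diastolic ≥ 90, but below 160/100, for 1 month.

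**Off-drug experimental patient, reading sustained for 1 month in follow-up**

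| Reading (mmHg) | Adjustment section | Follow-up as printed | (a) Sign reversed | (b) Lower bound added |
|---|---|---|---|---|
| 130/80 | stay off | advise drugs at 1 month | silent | silent |
| 150/95 | restart at 1 month | advise drugs at 1 month | silent | advise drugs at 1 month |
| 165/95 | add drug at 3 days | advise drugs at 1 month | advise drugs at 1 month | silent |
| 155/105 | add drug at 3 days | advise drugs at 1 month | advise drugs at 1 month | silent |
| 165/105 | add drug at 3 days | silent | advise drugs at 1 month | silent |

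**Reading the table**
1. At 130/80 the two sections give opposite instructions. The same holds at 110/70, 120/80 and 135/85. At these readings both components are under the limits, so the result does not depend on how the and/or is read.
2. At 150/95 the two sections agree.
3. At 165/95 and 155/105 both lead to drugs, but the adjustment section acts first.
4. At 165/105 the follow-up rule is silent, and the adjustment section covers the patient.
5. Repair (a) removes the conflict at 130/80 but leaves two waiting times at the same 160/100 limits: about 30 days against 3, and 30 / 3 = 10, so roughly tenfold.
6. Repair (b) matches the experimental restart rule. Because no arm is named, it would also apply to controls, for whom the adjustment section has no step below 160/100. Controls enter in just this band while already on one drug (Background; inclusion and exclusion criteria).

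**How many patients**

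480 patients randomised 1:1 gives 480 / 2 = 240 in the experimental arm. The article does not give the share who will be off drugs. For assumed shares:
- 10%: 0.10 × 240 = 24
- 25%: 0.25 × 240 = 60
- 50%: 0.50 × 240 = 120

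**The case against.** The best defence has four parts.

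**The conflict is partly inferred.** By follow-up the needling is over, so no one is then on acupuncture alone. The stop and restart sentences do not name follow-up, and a restart trigger does not expressly forbid drugs at other times. It is true that the contradiction is less explicit than it could be. But the restart rule has no end date, and the design section extends the adjustment rules over the whole study. A site would reasonably carry them into follow-up.

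**The intended rule is easy to guess.** With a lower bound of 140/90, the follow-up sentence repeats the experimental restart rule: same patients, same month, same action. Controls, already on one drug and with no stop rule, might see little change. This is a plausible repair, and the tenfold difference in waiting time belongs only to the other one. But the article does not choose between them, and they lead to different care at 150/95 and at 165/105.

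**The safety consequence is small.** This stands. The three-day rule covers readings at or above 160/100 in both arms, including in follow-up. What remains is recorded advice, not a prescription, to controlled patients who are off drugs.

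**The counts are not evidence.** This stands too. The shares are assumptions. With the projected 15% dropout the base would be 240 × 0.85 = 204, giving about 20, 51 or 102. A patient must also stay below 140/90 off drugs for a month after acupuncture ends, so even these are upper figures for each assumed share.

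None of this makes the printed threshold right, and no other part of the article corrects it.

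**Conclusion.** The concern holds. The follow-up threshold is wrong as written, and it contradicts the adjustment rules for experimental patients who are controlled below 140/90 without drugs. The error is more than clerical, because the sentence decides treatment within the primary-outcome window and its two natural corrections are not equivalent.

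Its reach is limited. High readings remain covered, the two sections agree for an off-drug experimental patient between 140/90 and 160/100, and the randomised 12 weeks of added acupuncture is complete before the rule applies. No effect on recurrence has been shown. The conclusion rests on one reading of scope, that the stop and restart rules continue into follow-up. The number affected cannot be derived from the article. This is a contradictory co-intervention rule that should be corrected, not an absence of safety rules.

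**What to change.** Delete the threshold in the Follow-up section and refer to the adjustment section, with its rules restated by arm for follow-up:

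- Experimental patients off drugs: restart the prior drug at systolic ≥ 140 and/or diastolic ≥ 90 mmHg for 1 month.
- Both arms: add a drug at systolic ≥ 160 and/or diastolic ≥ 100 mmHg for three days.

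If a separate follow-up rule was intended, state its lower bound, the arm it applies to and its duration, so that it does not conflict with the adjustment section.

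The cost is one protocol correction, an ethics notification and a memo to the five sites.

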### Outcome assessments

The assessors are blinded to grouping. The primary outcome will be all cases of recurrent stroke over a follow-up period of 9 months after receiving 12-week acupuncture treatments. Secondary endpoints, such as 24-h ambulatory BP, TCM syndrome score, Short Form 36-item Health Survey (SF-36) results, National Institute of Health Stroke Scale (NIHSS) and Barthel Index (BI) scale scores will be assessed at baseline, 6 weeks, and 12 weeks post initiating treatments; serum nitric oxide (NO), endothelin (ET), homocysteine (Hcy), soluble CD40 ligand (sCD40L), and copeptin levels and cardiac ultrasound, carotid artery ultrasound, transcranial Doppler, and lower extremity ultrasound results will be evaluated at baseline and 12 weeks after treatment. Other safety indicators including baseline general physical examination, blood, urine, and stool routine tests, coagulation function, D-dimer level, liver and kidney function, electrocardiograph as well as a chest X-ray will also be examined 12 weeks after randomization. At 6 months after randomization, blood, urine, and stool routine tests, coagulation function, D-dimer level, liver and kidney function, electrocardiograph, NO, ET, Hcy, sCD40L, and copeptin tests will be re-checked, with some hope of improving patients’ adherence to treatment. All-cause mortality will also be evaluated during the follow-up period. The Essen Stroke Risk Score (ESRS) will be additionally assessed at baseline and 1 year post randomization.

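### The follow-up rule advises antihypertensives at BP at or below 160 and/or 100 mmHg, with no lower limit and no arm named, and so contradicts the adjustment rule for experimental patients off drug

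*Protocol article*

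**What the plan says.** Two sections of the protocol article say when antihypertensive drugs change.

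**Antihypertensive medication adjustment.** In the experimental group, a mean BP below 140/90 mmHg for three days takes the patient off drug: "they will receive solely acupuncture treatment; thereafter, once their BP levels increase to ≥ 140 mmHg systolic" and/or 90 mmHg diastolic "for 1 month, prior antihypertensive medications should be re-dispensed". At 160 mmHg systolic and/or 100 mmHg diastolic or more for three days, after acupuncture has started "or over the follow-up period, additional antihypertensives should be prescribed". Control patients have the same 160/100 mmHg, three-day trigger throughout the study period, and the choice of other drugs is left to the treating physician.

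**Follow-up.** The trigger is "If the BP is ≤ 160 mmHg systolic and/or ≤ 100 mmHg diastolic for 1 month", and the action is that "the patient will be advised to take antihypertensive medications, which will be documented in the CRF". The sentence has no lower limit and does not say which arm it concerns.

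Three further statements bear on how the two fit together. Study design and setting says: "During the whole process of our study, the antihypertensive medications will be adjusted based on the BP level in the two groups", and points to the adjustment section for details. Background gives the reason for stopping the drug: "the prior antihypertensive drugs will be ceased, so as to observe the clinical effects of pure acupuncture on BP". Outcome assessments defines the primary outcome as "all cases of recurrent stroke over a follow-up period of 9 months" after the 12 weeks of acupuncture.

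**The concern.** A rule that starts or restarts antihypertensive treatment should act when BP is too high. This one is written to act when BP is at or below a limit, so it includes patients whose BP is controlled. For experimental patients who have come off their drug, it asks for the opposite of what the adjustment section asks.

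The sentence applies after acupuncture ends, which is when recurrent strokes are counted and when BP is recorded at weeks 24 and 48 (Table 1; 6 months and 1 year in Sample size and statistical methods). If one centre follows the Follow-up sentence and another the adjustment section, similar patients in the same arm could be on or off drug during that time. BP control is the route by which the trial expects to reduce recurrence, so the threshold for drug treatment in that window should have one meaning.

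**Working it through.** No sample size or power figure enters this point. The check applies each rule to one BP value per range, held for 1 month.

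**Inputs**
- Adjustment section, experimental patient off drug: stays off below 140/90; prior drug again after 1 month at ≥ 140 and/or ≥ 90; additional drug after three days at ≥ 160 and/or ≥ 100.
- Follow-up section, literal: advise drug after 1 month at ≤ 160 and/or ≤ 100, with and/or read as inclusive.
- Repair A: the sign is reversed (≥ 160 and/or ≥ 100 for 1 month).
- Repair B: a 140/90 lower limit is supplied (140–160 and/or 90–100 for 1 month).

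**Experimental patient off drug**

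| BP (mmHg) | Adjustment section | Follow-up, literal | Repair A | Repair B |
|---|---|---|---|---|
| 130/80 | stay off | advise drug at 1 month: **contradiction** | silent | silent |
| 150/95 | prior drug at 1 month | advise drug at 1 month: agrees | silent | advise drug at 1 month: agrees |
| 165/85 | add drug at three days | advise drug at 1 month, through the diastolic limb: same direction, later | advise drug at 1 month: later | silent |
| 170/105 | add drug at three days | silent | advise drug at 1 month: later | silent |

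**Controlled patients.** 120/75, 130/80 and 139/89 all meet the literal trigger. None of them meets a restart or add-on trigger in the adjustment section.

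**Reading and/or as and.** Controlled patients are still covered. In addition, 170/95 and 155/110 now fall outside the rule.

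**Both limits exceeded.** The literal rule says nothing at 170/105. The adjustment section still acts there in both arms, so this is a gap in the sentence and not a second contradiction.

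**Repair A.** The direction becomes right, but the same 160/100 threshold then carries two waiting periods: 1 month in one section and three days in the other.

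**Repair B.** This gives the adjustment section's re-dispense rule, with the same 1-month duration, and stops about where the three-day rule takes over. It fits only experimental patients off drug. A control patient at 150/95 is already on one drug, and the adjustment section changes nothing for that patient below 160/100. The sentence, which names no arm, would still address that patient.

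**What the rule can reach in time.** Acupuncture ends at week 12 and the sentence applies after that. Week 24 is 24 − 12 = 12 weeks later and week 48 is 48 − 12 = 36 weeks later. A 1-month rule can therefore act before both BP time points and inside the 9-month recurrence window. Table 1 places 24-h ambulatory BP at baseline, week 6 and week 12 only, all before the sentence applies.

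**The case against.** The strongest reply is that this is a clerical slip with a recoverable meaning. A dropped 140/90 lower limit gives a largely coherent rule. Control patients already take one drug, so advice to take antihypertensives has new effect mainly for patients off drug, and under the adjustment section those are experimental patients. This stands in part: a reader might infer that no correction can make the sentence fit, and that goes too far. But the sentence names no arm, the reversed sign is an equally natural guess, and the two repairs give different rules. No other section says which was meant.

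A second reply is that the stop-and-restart rule belongs to the treatment period, because a state of acupuncture alone has no clear meaning once acupuncture has ended. Only the 160/100 clause for the experimental group names follow-up. This weakens the conflict without removing it: the restart rule has no end date, and Study design and setting applies medication adjustment to the whole study. Even if the Follow-up sentence governed alone, advising drugs because BP is at or below a limit would still be wrong.

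A third reply is that all adjustments are recorded in the CRF and that staff are unlikely to act on a month of controlled BP. Both are fair. They limit the likely damage but do not correct the text.

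That a journal article condenses the full protocol excuses omissions. It does not excuse a stated threshold that conflicts with another.

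**Conclusion.** The Follow-up rule is wrong as written and should be fixed. Confidence in the textual conflict is high. It covers controlled patients, contradicts the adjustment section for experimental patients off drug below 140/90 mmHg, and is silent when both limits are exceeded.

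Its reach is drug use in the 9-month recurrence window and BP at weeks 24 and 48. Three stronger readings are not supported:

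- **That it defeats the aim of observing acupuncture alone.** Acupuncture and 24-h ambulatory BP both finish at week 12, before the sentence applies. The aim is touched only through later BP and the recurrence window.
- **That it cuts the drug-free time to about 1 of 9 follow-up months (1/9 = 11%).** This assumes a patient off drug at week 12, BP below 140/90 mmHg throughout, a month counted from week 12, and advice that is followed. The document fixes none of these. Nor is the single contradiction in the four rows of the table a measure of size, since the rows are test values chosen for the check.
- **That recurrence results are biased, or that severe hypertension goes untreated.** The document does not say how many patients stop their drug, and divergence between centres is possible but not shown. The three-day rule still covers high BP.

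The conclusion assumes only that the sentence means what it says and that the adjustment section applies for the whole study.

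**What to change.** Replace the Follow-up sentence with a cross-reference that restates the existing rules and adds no new policy, for example:

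> In follow-up, antihypertensive treatment is governed by the section Antihypertensive medication adjustment. An experimental patient off drug whose BP is ≥ 140 mmHg systolic and/or ≥ 90 mmHg diastolic for 1 month is given the prior drug again. At ≥ 160 mmHg systolic and/or ≥ 100 mmHg diastolic for three consecutive days, an experimental patient is given additional antihypertensives, and a control patient is given other antihypertensives as the treating physician judges.

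The last clause matters, because the adjustment section leaves the choice of drugs for control patients to the physician and the correction should not remove that. The CRF and the telephone follow-up form should carry the same text.

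The cost is small: one passage of text, a submission to the ethics committee (Ethical issues requires this for any protocol change) and a check of the two forms. The one real burden is retrospective. If any centre has already restarted a drug under the present wording, those restarts must be found in the CRFs and marked as such.

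### The Follow-up section's antihypertensive drug rule is wrong as printed and contradicts the medication-adjustment section that governs it

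*Protocol article*

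**What the plan says.** The Follow-up section covers the monthly telephone contacts up to one year after randomization. Without distinguishing the arms, it takes a BP at or below 160 mmHg systolic and/or at or below 100 "mmHg diastolic for 1 month, the patient will be advised to take antihypertensive medications".

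The Antihypertensive medication adjustment section sets four rules:

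- Stop, experimental arm only: "if the patients have a mean BP level below 140/90 mmHg for three consistent days, they will receive solely acupuncture treatment".
- Restart, experimental arm after a stop: BP ≥140 mmHg systolic and/or ≥90 mmHg diastolic "for 1 month, prior antihypertensive medications should be re-dispensed". No end date is given.
- Add, experimental arm: BP ≥160 and/or ≥100 mmHg for three days after the start of HuoXueSanFeng "acupuncture treatments or over the follow-up period, additional antihypertensives should be prescribed".
- Add, control arm: the same limits, "lasting for three continuous days in the study period, other antihypertensive drugs will be prescribed in the opinion of the treating physicians".

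The Study design and setting section says that throughout the study "the antihypertensive medications will be adjusted based on the BP level in the two groups", and sends the reader to the adjustment section for the details. The Background points to the same section. It also says that in the experimental arm, once BP is under 140/90 mmHg, "the prior antihypertensive drugs will be ceased, so as to observe the clinical effects of pure acupuncture on BP".

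Both needling regimens last 12 weeks (Experimental group; Control group). The primary outcome is recurrent stroke over the 9 months after that (Outcome assessments).

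**The concern.** A rescue rule should call for treatment when pressure is high. This one calls for it when pressure is at or below a limit, and nothing else in the article corrects it. The sentence is operative text for the period in which the primary outcome is counted, and it stands in the section that describes the follow-up calls.

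Someone working from that section alone would advise drugs for a controlled patient and give no advice when both pressures are high. Someone working from the adjustment section would do the opposite. The patients most exposed are experimental patients still off drug when needling ends. Only that arm has a stop rule, so only its patients can be taken off drug under the protocol and enter the outcome window with neither the drug nor the BP-lowering needling. From then on, BP triggers alone decide when treatment returns.

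**Working it through.** No figure in the plan rests on this rule, so the check is logical. Let S be systolic and D diastolic pressure in mmHg.

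**Inputs**

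- Follow-up section, as printed: (S ≤ 160) and/or (D ≤ 100) for 1 month → advise drugs.
- Adjustment section, experimental patient off drug: (S ≥ 140) and/or (D ≥ 90) for 1 month → restart the prior drug.
- Adjustment section, both arms: (S ≥ 160) and/or (D ≥ 100) for three days → add drugs.

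**Step 1: the rule as printed.** If either condition is enough, the rule fails only when S > 160 and D > 100 together. If both are required, it holds whenever S ≤ 160 and D ≤ 100. Under either reading 120/75 triggers advice (120 ≤ 160 and 75 ≤ 100) and 170/105 does not (170 > 160 and 105 > 100). The reversal does not depend on how and/or is read.

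**Step 2: side by side.** The four pressures illustrate the rules and are not frequencies. The patient is in the experimental arm, off drug, in follow-up. Either condition is taken as enough.

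| BP | Adjustment section | Follow-up, as printed | Follow-up, with ≥ | Follow-up, with a 140/90 floor added |
|---|---|---|---|---|
| 120/75 | no drug | advise at 1 month | no advice | no advice |
| 150/95 | restart at 1 month | advise at 1 month | no advice | advise at 1 month |
| 170/95 | add after three days | advise at 1 month | advise at 1 month | advise at 1 month |
| 170/105 | add after three days | no advice | advise at 1 month | no advice |

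**Step 3: reversing the sign.** With ≥, the rule becomes (S ≥ 160) and/or (D ≥ 100) for 1 month. These are the adjustment section's own limits for adding drugs, with one month in place of three days, in both arms. Silence at 150/95 is not in itself a contradiction, because the adjustment section still acts there. The timing is.

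**Step 4: adding a floor.** The rule becomes (140 ≤ S ≤ 160) and/or (90 ≤ D ≤ 100) for 1 month. It then matches the adjustment section at 120/75 and 150/95 and leaves 170/105 to it. What overlaps is the exact limits (160 or 100) and mixed readings such as 170/95, where D = 95 meets the one-month rule and S = 170 meets the three-day rule.

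**Step 5: when it bites.** Inclusion requires a stroke more than 2 and less than 6 weeks old. Twelve weeks of needling therefore end about 2 + 12 = 14 to 6 + 12 = 18 weeks after the stroke, ignoring any delay between screening and the first session. The 9-month outcome window starts there.

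**The case against.** The strongest reply is that the sentence is a slip and the rest of the article shows what was meant. Much of this stands.

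- **Precedence.** Two sections send the reader to the adjustment section, and that section says it covers follow-up. A reader might infer two rules of equal standing with nothing to choose between them. The documents do not support that. The pointers do not cancel the Follow-up sentence, however, and a site has no text telling it to disregard the sentence.
- **An omitted floor.** The inclusion criteria give only an upper limit of 160/100 mmHg. The 140/90 floor appears in the exclusion criteria and in the Background, where "we cautiously decided to select the hypertensive patients with uncontrolled BP" is followed by both bounds. The one-month duration equals that of the restart rule, and advice to take drugs suits a patient who is off them. This makes a missing floor plausible, but it remains an inference.
- **Week 12.** A reader might infer that off-drug patients are left without any instruction when needling ends. They are not: the restart trigger is open-ended, so the default is to stay off drug until it is met. Preferring that drugs resume at week 12 is a design choice, not a correction.
- **The stop rule.** A reader might think it carries on into follow-up. Its wording assumes that needling is still being given, so no defect is shown there.
- **Patients already on drug.** For them, advice to take drugs changes little at 120/75. The literal fault at that pressure mainly concerns off-drug experimental patients.
- **Training.** Central training is planned and may prevent divergence between sites. Whether sites would in fact diverge cannot be shown from the article.

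**Conclusion.** The Follow-up sentence states a wrong treatment threshold and should be corrected. The reversal at 120/75 and 170/105 follows from the printed text under either reading of and/or, and needs no assumption. Changing the sign alone would not bring the sentence into line with the adjustment section. Adding a floor nearly would, but the authors would have to say so.

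The size of the consequence is unknown. The documents do not give the share of experimental patients off drug at week 12, and none is assumed here. A reader might go further and conclude that the primary comparison is biased or invalid. The documents do not support that: they show neither size nor direction of any effect on recurrence, and the Background openly discloses that drugs are stopped in one arm of a pragmatic trial. The reason to act is patient safety and uniform conduct in patients with a recent stroke, during the period in which the primary outcome is counted.

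**What to change.** Replace the drug-advice sentence in the Follow-up section with the adjustment section's triggers, for example:

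> During follow-up the triggers of the adjustment section apply. An experimental patient who is off drug restarts the prior drug when BP is ≥140 mmHg systolic and/or ≥90 mmHg diastolic for 1 month. In either arm, drugs are added when BP is ≥160 mmHg systolic and/or ≥100 mmHg diastolic for three days. These triggers are unchanged after needling ends at week 12.

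This keeps the thresholds and durations the protocol already has. The cost is a short protocol clarification, submitted to the ethics committee as any protocol change must be. It needs no new visits and no new data, since the BP diary and the medication records in the CRF already supply what the triggers require.
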